## Abstract

**Background:**

Stroke affects over 1 million people in Europe and 25,000 in Sweden annually, with high mortality and disability rates. Dysphagia, a common post-stroke issue, occurs in over 50% of patients in the acute phase. Evidence-based studies are lacking on rehabilitative interventions to improve post-stroke dysphagia. Current management focuses on compensatory strategies, but oral neuromuscular training shows promising results. Challenges to rehabilitation programs include poor adherence and the need for effective monitoring technologies. The primary objective of the current trial is to investigate the impact of oral neuromuscular training with a sensor-equipped oral device on post-stroke dysphagia.

**Methods:**

This national, multicenter, investigator-initiated, randomized, parallel-group trial compares the effect of oral neuromuscular training versus standard care in patients with post-stroke dysphagia. We will enroll 336 consecutive participants who have no prior history of dysphagia and exhibit persistent dysphagia 3 months following the onset of ischemic stroke or intracerebral hemorrhage. Participants will be randomly assigned in a 1:1 ratio to receive either a 12-week intervention consisting of standard routine care combined with oral neuromuscular training (using an oral device with sensors for adherence feedback) or current routine care alone. Standard routine care includes compensatory strategies such as bolus modification, adapted swallowing postures, and maneuvers. The primary outcome is the degree of dysphagia at end of intervention, assessed with Flexible Endoscopy Evaluation of Swallowing (FEES) by blinded evaluators, and analyzed with ordinal regression models. Secondary outcomes are changes in nutritional status, pneumonia, mortality, and quality of life after a 12-week intervention and at 6-month follow-up.

**Discussion:**

This first randomized clinical trial in stroke rehabilitation on neuromuscular oropharyngeal training with sensors to facilitate adherence and comprehensive outcome measures will enable evaluation of this treatment with the potential for significant clinical impact for patients with dysphagia after stroke.

**Trial registration:**

ClinicalTrials.gov, identifier: NCT02960737. First registered on 11 November 2016 and later modified to the present multicenter study design on 22 August 2023.

## Introduction

### Background and rationale {9a}

Stroke is a major public health issue, affecting over 1 million people in Europe and 25,000 in Sweden each year, with deaths in one-fifth and persistent disability in almost half of the survivors [1]. It is the second leading cause of death worldwide and the foremost contributor to dysfunction and disability among adults. Common post-stroke complications include hemiparesis, sensory loss, aphasia, dysphagia, hemianopia, and neuropsychological symptoms. In Europe, stroke care costs are estimated to rise from €60 to €86 billion by 2040, with Oxford University suggesting actual costs may be higher due to excluded social and home care services [2]. In Sweden alone, the societal cost of strokes surpasses €1.8 billion each year, placing significant pressure on the healthcare system.

*Post-stroke dysphagia*: Dysphagia refers to difficulties in swallowing and transporting food, drink, saliva, and medications from the mouth to the stomach. Stroke is considered the leading cause of dysphagia among adults, with an estimated incidence of over 50% in the acute phase [3]. Dysphagia is further reported in 17% of patients at 28 days [4] and in 10–15% at 6 months after a stroke [5]. Dysphagia is related to various secondary complications, including malnutrition, dehydration, and aspiration pneumonia, resulting in impaired life quality and increased risk of early mortality [3, 6, 7].

During the acute phase of a stroke, guidelines recommend that all patients undergo a swallowing assessment using a validated screening tool prior to any oral intake [8–11]. If dysphagia is suspected, a thorough evaluation should be performed using Flexible Endoscopic Evaluation of Swallowing (FEES) [10]. This approach is essential for ensuring accurate diagnostics, as instrumental assessments are acknowledged for their superior sensitivity in detecting dysphagia.

Current approaches to managing post-stroke dysphagia primarily focus on compensatory strategies, such as adjusting head and neck posture and modifying the consistency of food and fluid intake [12]. While these methods can help mitigate the risk of aspiration, they do not address the underlying swallowing impairment. In severe cases, patients may require artificial nutrition through feeding tubes, which is associated with increased care demands, hospitalization, and costs.

Various attempts with direct intervention on swallowing physiology and post-stroke dysphagia with rehabilitative strategies such as pharyngeal electrical stimulation, tactile stimulation, transcranial direct current stimulation, and transcranial magnetic stimulation have all been without significant positive effects [12, 13]. Oral neuromuscular training with an oral device is a promising alternative. A small randomized controlled trial showed improvement in post-stroke dysphagia [14], and positive results have been observed among older people with dysphagia [15].

This intervention aims to directly improve swallowing physiology and function, potentially offering a more effective solution than compensatory strategies alone. However, larger, more rigorous clinical trials are needed to establish the efficacy of this novel approach. This area is highlighted for research and development in the Swedish National Stroke Guidelines, underscoring its importance.

One of the major challenges in managing post-stroke dysphagia is the low adherence to rehabilitation programs. Studies have reported that less than 50% of patients maintain engagement with home-based stroke therapy within the first month after hospital discharge [16]. Improving adherence is crucial, as it is directly linked to better patient outcomes and reduced healthcare costs. To address this issue, researchers have explored the use of sensor technologies. These technologies provide real-time monitoring of patient adherence, potentially enabling more accurate tracking and support for patients while minimizing the risks associated with biased or inaccurate self-reporting [17].

Post-stroke dysphagia presents significant challenges requiring effective, evidence-based interventions to enhance swallowing function and mitigate associated risks. Continued research into novel treatment strategies and adherence monitoring is crucial to address these unmet needs and improve outcomes for stroke survivors.

### Explanation for the choice of comparator {9b}

Compensatory strategies are considered standard care for post-stroke dysphagia [12].

### Objectives {10}

The primary objective of this study is to investigate the effect of a 12-week intervention with an oral neuromuscular training device in stroke patients with persistent dysphagia in the sub-acute phase. Secondary objectives are to investigate the treatment effect on aspiration pneumonia, swallowing-related quality of life, and death.

## Methods: patient and public involvement, and trial design

### Patient and public involvement {11}

Patient and public involvement has played a central role in the development of this trial. Years of clinical experience and ongoing dialogue with individuals with post-stroke dysphagia as well as their relatives have highlighted the substantial impact of dysphagia on daily life, social participation, and overall well-being, underscoring the importance of user involvement to optimize treatment adherence and outcomes. To improve the study design, feedback was collected from patients and relatives, and contact was established with regional stroke associations at participating sites. Patient representatives have been recruited to the Steering Committee ensuring continuous patient input throughout the planning, conduct, and evaluation phases of the trial. Their contributions have directly shaped key aspects of the study, including refinement of the training method, incorporation of a sensor to support compliance, involvement of relatives in the treatment process, and extension of the training period to 3 months based on user-reported needs and clinical experience. In response to patient preferences for continued follow-up, a 6-month post-treatment assessment has also been incorporated. Patient representatives will remain actively involved throughout the trial to ensure that the study remains aligned with patient priorities and experiences.

### Trial design {12}

The DESIRE is designed as a multicenter, national, investigator-initiated, randomized, parallel-group, superiority trial to compare the effect of 12-week oral neuromuscular training versus standard care in patients with persistent post-stroke dysphagia and with the primary endpoint of degree of swallowing dysfunction immediately after the intervention period.

## Methods: participants, interventions, and outcomes

### Trial setting {13}

Participants will be recruited from multiple sites across Sweden, including academic and regional hospitals and outpatient clinics, to achieve the target sample size. To date, recruitment of participants is ongoing at nine sites. Further sites will be recruited. Study assessments will take place at each site or at a healthcare center close to the participant’s home, whereas the intervention will be performed daily by the participant in their home or care unit/nursing home.

### Characteristics of the people who are needed for the trial

The expected characteristic of the people that will be included in the study is displayed in Table 1.

**Table 1 Tab1:** Expected demographic characteristics of the participants

Characteristic	The people we would expect to see included
Age	Individuals aged 18 years and above; with mean age 75 based on age distribution in the Swedish National Stroke Registry [1]
Sex	Female and male
Gender	Both women and men; with a slightly higher proportion of men, consistent with sex distribution in the Swedish National Stroke Registry [1]
Race, ethnicity, and ancestry	Predominantly individuals of European descent, reflecting the Swedish population; minority representation expected to be low based on national demographics
Socioeconomic status	Participants from varied socioeconomic backgrounds; distribution expected to reflect national patterns, with most in middle-income categories
Geographic location	Nationwide recruitment including rural, suburban, and urban areas across southern, central, and northern Sweden
Other characteristics relevant to the trial	Not applicable

### Eligibility criteria for participants {14a}

Eligibility criteria are consecutive patients with stroke (ischemic or hemorrhagic) with persistent dysphagia (defined as Dysphagia Outcome Severity Scale, DOSS, ≤5 on FEES assessment) [18, 19] at 1–3 months (4–12 weeks) post-stroke onset. Exclusion criteria: previously known dysphagia; unable or unwilling to give informed consent or to cooperate. The study inclusion and procedure are depicted in Fig. 1.

**Fig. 1 Fig1:**
[figure not shown]
Study inclusion and procedure of the DESIRE study. *The same assessments are performed at baseline as at 12 weeks (post-intervention) and 6 months post-intervention. Abbreviations: DOSS = Dysphagia Outcome Severity Scale; FEES = Flexible Endoscopic Evaluation of Swallowing; MNA = Mini Nutritional Assessment; SWAL-QOL = Swallowing Quality of Life Questionnaire; mRS = modified Rankin Scale

### Eligibility criteria for sites and those delivering interventions {14b}

Eligibility criterion for individuals who will perform the assessments is that they are trained in the consent process, study protocol, and are FEES competent (i.e., speech-language pathologist and/or otolaryngologist).

### Who will take informed consent? {32a}

Trained investigators at each site will introduce the trial to patients at the standard FEES assessment at 1–3 months post-stroke, providing them with written information about the study. Subsequently, the investigators will facilitate discussions about the trial, giving patients the opportunity to ask questions and seek clarification on the provided materials. The investigators will be certified in Good Clinical Practice (GCP) [20] and the Declaration of Helsinki [21].

For patients with aphasia or those unable to write after a stroke, verbal consent will be sought for participation, as witnessed by an independent observer such as a staff member, relative, or friend, who will then sign and date the form.

### Additional consent provisions for collection and use of participant data and biological specimens {32b}

N/A as we will not collect biological specimens in this trial and no additional study is planned. Any future use of participant data beyond the scope of this protocol would require new ethical approval and additional consent.

## Intervention and comparator

### Intervention and comparator description {15a}

The intervention group will be given intensive oral neuromuscular training of orofacial and pharyngeal muscles with an oral device (IQoro® Myoroface, Sweden). Oral neuromuscular training involves enhancing sensory input and strengthening the facial, oral, and pharyngeal muscles. An oral device is positioned pre-dentally behind closed lips and is then pulled straight forward for a duration of 5–10 s, keeping the device in place with the lips by activating the orofacial, oral, and pharyngeal muscles (see Fig. 2). This exercise is repeated three times, with a rest period of 3 s between each repetition. The training is conducted three times daily, for 12 weeks. Additionally, the intervention group will receive individualized compensatory strategies equivalent to those provided to the control group.

**Fig. 2 Fig2:**
[figure not shown]
Oral neuromuscular training (left). The device is placed pre-dentally behind closed lips. The device is then pulled straight forward for 5–10 s, keeping the device in place with the lips by activating the orofacial, oral, and pharyngeal muscles. The training is repeated three times, with a 3-s rest in-between. Oral device (right)

The control group will be given individualized instruction on compensatory strategies to compensate for their specific swallowing dysfunction. For example, posture considerations for head, neck, and body during swallowing, swallowing maneuvers, and modification of bolus volume, consistency, and texture.

### Criteria for discontinuing or modifying allocated intervention/comparator {15b}

There are no provisions for modifying the allocation of trial arms. Participants have the right to withdraw from the study at any time without providing an explanation, and their future care will remain unaffected. All data collected prior to withdrawal will be retained and included in the analyses.

### Strategies to improve adherence to intervention/comparator {15c}

To improve participant adherence, a sensor is attached to the oral device to register the treatment compliance/adherence, i.e., the frequency (newton) and duration (seconds) of training—which will give feedback to the investigator, the patient, and for data collection. Frequency and duration of the training is registered while the participant is using the oral device and is uploaded via an app using Bluetooth for feedback on the training session.

### Concomitant care permitted or prohibited during the trial {15d}

Throughout the trial, participants in both groups will not be allowed to employ any other active training methods, except for modifying food consistencies to enhance swallowing.

### Ancillary and post-trial care {34}

No formal post care provision is planned in the study. Participants with persistent dysphagia at follow-up 6-month post-intervention (i.e., 12 months post-stroke) will be treated according to the clinical routine at each site.

### Outcomes {16}

#### Primary outcome

Post-intervention degree of swallowing dysfunction, measured immediately after the completion of the 12-week oral neuromuscular training intervention or use of compensatory strategies (end-of-treatment assessment); examined transnasally with a FEES, assessed using the DOSS [18, 19]. DOSS is an internationally widely used scale for measuring swallowing safety and efficacy on an ordinal scale and is based on the International Classification of Functioning, Disability and Health (ICF) classification. DOSS lists objective criteria on a 7-point Likert scale to systematically rate the functional swallowing severity from 1 (severe dysphagia and total dependency of artificial nutrition) to 7 (normal swallowing function and normal diet) based on symptoms observed during a FEES and impact on eating/drinking function. Subsequently, the DOSS results are directly transferable into recommendations for the patients regarding the diet level (tube feeding, modified diet, or no restriction), independence level (grade of assistance during mealtime), and type of nutrition the patient can swallow safely (liquid, thickened bolus, etc.). The scale has shown high validity and excellent inter- and intra-rater reliability [18, 19]. To account for participants who are too fragile to undergo the FEES examination, a composite variable strategy [22] will be employed to mitigate bias. Specifically, if a DOSS score is missing because a participant is judged to have severe swallowing dysfunction or frailty preventing assessment, a DOSS value of 0 (representing the worst outcome) will be imputed. This procedure is described in greater detail in the section: “Methods in analysis to handle protocol non-adherence and any statistical methods to handle missing data.”

#### Secondary outcomes

The intervention and the control group will be compared at end-of-treatment and at 6-month follow-up, adjusted for baseline values on the following secondary outcomes:Nutritional status [23] is measured with the Mini Nutritional Assessment Short Form (MNA-SF). The MNA-SF contains 6 items with a total score ranging from 0 to 14; a score of ≥12 points indicate that a person is well-nourished, 8–11 points indicate a risk of malnutrition, and <7 points indicate that the person is malnourished. MNA has been shown to have high sensitivity and specificity (96% and 98%, respectively) and significant agreement between observers (*K* = 0.51) and the MNA-SF has been shown to be a stand-alone nutritional assessment. The total score will be analyzed as an ordinal variable without categorization and compared between group.Swallowing-related quality of life is measured with the Swallowing Quality of Life Questionnaire (SWAL-QOL) [24], which is a patient-reported outcome measure (PROM) and consists of 44 items on a 5-point Likert scale that assesses 10 quality-of-life concepts: burden, eating duration, eating desire, food selection, communication, fear, and mental health. It further contains a dysphagia clinical symptom scale (symptom score). Scores for each domain are calculated using a linear transformation to a total test score ranging from 0 to 100, with higher scores indicating better quality of life. The Swedish version of SWAL-QOL has high internal consistency, high validity, and excellent test-retest reliability. The total score will be treated and analyzed as an ordinal variable without categorization and compared between groups.Rate of aspiration pneumonia based on the modified criteria by Centers for Disease Control and Prevention (CDC) for stroke-associated pneumonia [25]. The data are collected through patient reports and records. The incidence of aspiration pneumonia will be compared between groups.Lip force [26] assessed with a device measuring the lip force in newton (N). The maximum value (best of three trials) will be treated as a continuous variable and compared between groups.Functional status measured with (a) the Barthel index (BI) [27] which is an ordinal scale that consists of 10 items measuring a person’s functional independence on activities in daily living (ADL): bowels, bladder, toileting, bathing, eating, dressing, grooming, transfer, stairs, and ambulation. The scale ranges from 0 to 100. BI is widely used within both stroke care and research, and it is sensitive enough to detect improvement in function after stroke as well as having good reliability between administrators. Functional status is also measured by (b) the modified Rankin Scale (mRS) [28], which is a 7-point scale ranging from 0 (no symptoms) to 6 (death). The mRS has shown high validity and reliability when tested among patients with stroke. BI and mRS total scores will be analyzed as ordinal variables without categorization and compared between groups.Death: The mortality rate will be compared between groups.

### Harms {17}

Although no significant adverse events are anticipated during the trial, there may be instances of muscle pain affecting the orofacial and pharyngeal muscles after training with an oral device. All adverse events, including both expected and unexpected events, will be collected throughout the study period. Harms will be collected systematically at the end of the treatment period using structured questioning, and non-systematically through spontaneous reporting if participants contact the site investigator during the trial. At study initiation, participants will be instructed to promptly notify the site investigator by telephone if any adverse event occurs.

Investigators at each study site will document the nature, severity, duration, and relatedness of all reported adverse events. Adverse events will be coded according to the Medical Dictionary for Regulatory Activities (MedDRA) and graded according to Common Terminology Criteria for Adverse Events (CTCAE) to ensure consistent classification, analysis, and reporting across sites.

In the event of an adverse occurrence, the trial investigators will report the information to the project coordinator, principal investigator, and trial steering committee. The steering committee will subsequently notify the data monitoring committee, along with a tailored action plan. All adverse events collected during the trial, including non-serious and expected events, will be summarized and reported in study publications. Events classified as related and unexpected serious adverse events (RUSAEs) will be reported in accordance with regulatory requirements.

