### Participant timeline {18}

A schematic diagram of participant enrollment, interventions, assessments, and visits for participants is presented in Fig. 3. Each participant is involved for approximately 9 months (12 weeks intervention and 6 months follow-up period) (see Fig. 3). As a standard procedure, and according to national stroke guidelines, all patients with dysphagia in the acute phase of stroke are followed up with a FEES at 1–3 months after stroke onset. If persistent dysphagia is present, the patient is invited to participate in the study. After their written informed consent is obtained, the participant will be allocated to either intervention or control group. Based on the baseline FEES assessment (performed prior allocation, as part of routine procedure), the participant will receive individualized compensatory strategies. Assessments regarding secondary outcomes will be conducted after the participants have given their informed consent. Same assessments as at baseline are performed after 12 weeks (end-of-treatment) and 6 months later (follow-up). The first participant was enrolled on 26 February 2022, and the final participant is expected to be enrolled in July 2028, based on an estimated annual enrollment rate of 84 participants for the remaining study period.

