### Sample size {19}

Expected proportion of patients with dysphagia (i.e., DOSS ≤ 5) at follow-up in the control group is 65% [5]. We have dimensioned our study to detect a marginal odds ratio of 2 when using an ordinal proportional odds model. This corresponds to a proportion of patients with swallowing dysfunction of 52% in the intervention group. We expect a majority of patients to have a DOSS score of 5 or 6 at 12 weeks (end-of-treatment), based on clinical experience. Under the assumption of a marginal DOSS score distribution of 3%, 7%, 10%, 13%, 24%, 30%, and 13% for the DOSS score points of 1–7, respectively, 135 subjects are sufficient to detect an odds ratio of 2 with 90% power using an ordinal proportional odds regression model. Power calculations were performed using the function *popower*, from the R package Hmisc [29]. In the study, the odds ratio will be conditioned on the patients’ baseline DOSS score, as well as for the stratifying variables center and aspiration, which should provide further power compared to estimating a marginal odds ratio, as assumed in the power calculations. To account for a dropout rate of 20%, 168 patients will be recruited for each group.

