### Plans to promote participant retention and complete follow-up {25b}

Several strategies will be used to promote participant retention and complete follow-up. During the follow-up period, participants in both groups will be contacted 1 week after allocation for follow-up on their usual care regarding individualized compensatory strategies. The intervention group will also be followed up regarding their oral neuromuscular training (see “Intervention”) and asked if they have any questions or need assistance with monitoring the training. This keeps the participants in both groups engaged to follow the study procedures, promoting successful retention.

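### Structured questioning about harms is stated only at end of treatment, so most harms in the 6-month follow-up, and all harms in participants who leave before week 12, rest on spontaneous telephone reports

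*Protocol article*

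**What the plan says.** The Harms section states the scope first: "All adverse events, including both expected and unexpected events, will be collected throughout the study period". It then names two modes of collection: "Harms will be collected systematically at the end of the treatment period using structured questioning, and non-systematically through spontaneous reporting", the second applying "if participants contact the site investigator during the trial". The route for spontaneous reports is set at study start: "participants will be instructed to promptly notify the site investigator by telephone if any adverse event occurs". All adverse events collected are to be summarised in the publications.

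The length of observation is in the Participant timeline section: "Each participant is involved for approximately 9 months (12 weeks intervention and 6 months follow-up period"). The same section places a visit 6 months after end of treatment, at which the baseline assessments are repeated.

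Three other places bear on the point. The retention section describes an early contact: "participants in both groups will be contacted 1 week after allocation for follow-up on their usual care". It adds, for the intervention group only, follow-up of the training and an invitation to raise questions or ask for help. The section on discontinuing the intervention lets participants withdraw at any time and keeps the data gathered up to then; it mentions no enquiry on leaving. The consent section admits people with language impairment: "For patients with aphasia or those unable to write after a stroke, verbal consent will be sought for participation".

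**The concern.** How often an adverse event is found depends heavily on whether anyone asks. The plan asks once, at week 12. An event that is not asked about and not volunteered is absent from the data, and no analysis plan written later can recover it.

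This bears on three things. First, a participant who gives up the training because of discomfort and does not attend at week 12 is never asked, although such a participant may well have had a harm to report. Second, new or lasting complaints after week 12 are recorded only if the participant rings the site, even though a 6-month visit takes place anyway. Third, participants know their allocation, and at 1 week only one arm is spoken to about its training, so the opening to mention a complaint is not the same in both arms.

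At stake is the published comparison of adverse events, and the safety information that the data monitoring committee sees each year. The primary analysis is not affected.

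**Working it through.** **1. Length of observation.** Inputs: 12 weeks of intervention and 6 months of follow-up (Participant timeline).
- 6 months = 6 × 365.25 / 12 / 7 = 26.1 weeks.
- Total = 12 + 26.1 = 38.1 weeks, or 8.8 months. This reproduces the article's figure of about 9 months.
- Share after the only stated structured enquiry = 26.1 / 38.1 = 68%.

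The 68% is time after training has ended. It measures how long collection relies on spontaneous reports; it is not the share of harms missed.

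**2. Participants who could miss the enquiry.** Inputs: 336 participants, 168 per arm, and the planning assumption in the Sample size section: "To account for a dropout rate of 20%, 168 patients will be recruited for each group".
- 0.20 × 336 = 67.2, about 67 in total.
- 0.20 × 168 = 33.6, about 34 per arm.

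The article does not say how much of this dropout falls before week 12, or how many dropouts would miss the visit altogether. The lower bound is therefore 0 and the upper bound about 67.

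**3. What each contact covers, according to the text.**

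| Contact | Who | Structured harms questions stated? |
|---|---|---|
| 1 week | Both arms on compensatory strategies; intervention arm also on training | No |
| 12 weeks | Both arms | Yes |
| Withdrawal or stopping training | No enquiry described | No |
| 6 months after treatment | Both arms | No |

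**4. What is covered in follow-up by other means.** The Secondary outcomes section compares aspiration pneumonia and death between arms at end of treatment and at 6 months, with pneumonia taken from patient reports and records. These two are ascertained as outcomes, so the follow-up gap concerns the remaining adverse events.

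**5. Recall.** Orofacial and pharyngeal muscle pain is the one harm the plan anticipates. At the single enquiry it is recalled over up to 12 weeks.

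**6. Reporting route.** Outside week 12 the stated route is a telephone call by the participant. The text names no proxy, although the trial admits people with aphasia and the training may be done in a care unit or nursing home. That this route suits some of them poorly is a reasonable inference; the article does not address it.

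**The case against.** The strongest reply is that the plan is coherent as it stands. Spontaneous reporting is a form of collection, so promising to collect events throughout and asking systematically once is not a contradiction. The enquiry comes at the end of the whole exposure period, when training-related muscle pain would already have occurred, and nothing limits it to one arm, so it gives a comparable record for those who attend. The article is condensed and its schedule figure (Fig. 3) is not available; it may list adverse events at 6 months. All of this stands. It is why the point is an improvement rather than an error, and why confidence is no more than medium. It does not answer the lack of any enquiry on leaving, or the reliance on self-made calls after week 12.

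A reader might infer more than the documents support:

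- **That the whole follow-up phase is passive.** It is not. Pneumonia and death are outcomes at 6 months, and nutritional status, swallowing-related quality of life, Barthel index and mRS are also assessed then.
- **That the list of assessments in the data collection section shows harms are not asked about at 6 months.** One list serves all visits, and it omits harms at week 12 too, where the Harms section places the enquiry. Its silence proves nothing about month 6.
- **That participants with aphasia are left wholly to the telephone.** Those who attend at week 12 are questioned like everyone else. Patients unable to cooperate are excluded, and nothing bars a relative or care staff from calling.
- **That the training arm has extra contacts, so event counts will differ.** Both arms are contacted at 1 week; the intervention arm has extra content, not a stated extra contact. A difference in reporting is possible, not established.
- **That about 34 per arm will miss the enquiry.** This is the upper end. Some dropouts may leave after week 12 or miss only the FEES, and home assessment is provided for.

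**Conclusion.** The point holds in limited form. The text sets out to collect all adverse events for about 9 months and states structured questioning at one time only, end of treatment. Harms other than aspiration pneumonia and death during the last 26 or so weeks, and any harms in the 0 to about 67 of 336 participants who might leave before week 12, therefore rest on spontaneous telephone reports. The opportunity for such reports may differ by arm; the documents give no basis for estimating by how much.

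This rests on two assumptions: that the Harms section describes the full method, and that dropout is near the planned 20%. If Fig. 3 schedules harms questions at 6 months, the follow-up part becomes a matter of aligning the text, while the text would still name no enquiry on leaving and no proxy route. The label is a cheap improvement, minor in severity, with medium confidence.

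**What to change.** In the Harms section, specify one set of structured harms questions, identical in both arms, at contacts that already exist: the 1-week contact, the 12-week visit and the 6-month visit. Add one enquiry when a participant stops training or withdraws, if the participant agrees. State that a relative or care staff may report for participants who cannot telephone. If Fig. 3 already has harms questions at 6 months, bring the Harms section into line with it.

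The cost is a short form, a protocol amendment, a few minutes per contact and a higher count of mild events. No endpoint, sample size or alpha changes. Because the added contacts begin partway through recruitment, the report should say from what date they applied.

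The change is still worth making. Protocol version 4.0 is dated December 2025, recruitment is expected to run to mid-2028, and the estimated rate is 84 per year. About 2.5 × 84 = 210 of 336 participants would enter after that version, if the rate is met. The benefit shrinks with each month of delay.
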